### Data collection, management and analysis

#### Data collection methods

Primary and secondary outcome data will be collected at baseline and follow-up visits by research staff to schools, conducted during class time. Standing and sitting height and weight will be collected by trained research nurses from the Clinical Research Facility at the Southampton NIHR Biomedical Research Centre (SBRC). These measures will be used to derive body mass index *z*-scores and biological maturity [49]. All researchers and research nurses working on the EACH-B trial will be trained in trial-specific procedures and be required to complete appropriate safeguarding and eating-disorder training.

Questionnaire data will be collected through participant completion of questionnaires on iPads during the baseline and follow-up visits to schools. The class will be divided into small groups of 7–8 students working with one member of the research team who will act as a facilitator. Before students begin completing the questionnaires, the facilitator will use a trial-specific standard operating procedure to explain key points about the questionnaires and will remain with the group throughout the session to answer any questions that might arise.

GENEActiv™ accelerometers will be distributed to participants by trained research staff during the data collection sessions at both time points. The devices will be programmed to automatically start measuring at midnight on the first day of data collection and stop measuring precisely 7 days later, in order to capture both weekend and weekday activity. A sampling frequency of 100 Hz will be used. Participants will be asked to keep the device on their non-dominant wrist for seven full days, preferably without taking it off at any point. Seven days after the baseline data collection visit, schools will be asked to return the GENEActivs to the research team via courier or another secure method.

#### Data management

After data collection visits to schools, all data will be downloaded from the iPads via a Secure Sockets Layer (SSL) that encrypts the data before sending it and storing it in the database. The database itself is kept on a University server. All questionnaire data will be kept in accordance with General Data Protection Regulations (GDPR), University of Southampton Data protection policy and in accordance with the protocols of the MRC Lifecourse Epidemiology Unit LEU). The data will be stored in password-protected computers by the research team and only accessible by them. Data will be stored in Access databases and managed with support from the data management staff of the MRC LEU, who have extensive data management expertise and manage data from more than 200 studies. After the trial is complete, anonymised data will be available to other researchers under our data sharing protocols.

Identifying information will be collected about participants, purely for the purposes of matching baseline and follow-up questionnaires. All identifying information will be stripped from the rest of the data after linkage is complete and will be stored separately. It will only be kept in case a further follow-up is planned.

#### Statistical methods

Data will be analysed using Stata, SPSS and Mplus. The primary analyses will be according to the intention-to-treat principle, comparing dietary quality and PA levels in the intervention and control groups using mixed effects linear regression to account for clustering within schools. The main analysis will compare these outcomes at baseline and at 12 months follow-up. Although randomised at the level of schools using a minimisation algorithm, there may still be disparities between the intervention and control participants at baseline. These will be assessed prior to analysis and relevant confounders will be incorporated in the models; factors to be considered include gender, exact age at recruitment and household area of deprivation using the Income of Deprivation Affecting Children Index (IDACI) score [58]. Adjustment for baseline dietary quality and PA levels will be included in the relevant models to allow an assessment of change from baseline. Sensitivity analyses will examine effects of missing data, and multiple imputation will be used where appropriate, accounting for the clustered nature of the data.

Comparisons for secondary outcomes will also be modelled using mixed effects linear regression, with the use of binary models for binary outcome variables. Mixed effect logistic regression will be used for rare outcomes and mixed effect binary regression (or Poisson regression with robust variance if the binary regression models fail to converge) will be used for outcomes that occur in more than 10% of students. We will then conduct a mediation analysis to examine the role of these secondary factors in mediating the effect of the intervention on primary outcomes. The main analyses will be conducted using the latest available version of Stata.

Planned subgroup analyses will focus on whether there are different effects for boys and girls, differing ethnicities, seasonal variation, IDACI score and estimated biological maturity in outcomes. We will also determine the effect of EACH-B on outcomes for those who fully engage with the digital intervention (per protocol analysis) and assess uptake of the digital intervention by gender, ethnicity and IDACI score. Complier average causal effect (CACE) modelling techniques will be used to examine factors that predict engagement with intervention components and to examine intervention effects specifically for students who engaged with those components. As this is a cluster randomised controlled trial, many of the assumptions underlying this method are unlikely to be valid, most obviously the independence of the participants [59]. These assumptions will be assessed and methods of analysis developed appropriately. The CACE analysis will be performed using MPLus.

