### Sample size

Unpublished analysis of earlier data from LifeLab indicates an intra-school (class) correlation coefficient of 0.035. Forty-six schools each sending two classes amounting to approximately 50 students from each school and 2300 students in total will provide 90% power at a 0.025% significance level (accounting for two primary outcomes) to detect a 0.25 SD difference in diet quality score or minutes of total PA in intervention and control schools. Comparable effect sizes have been considered in other health interventions as meaningful in terms of change in health behaviours, and our level of 0.25 SDs falls in the mid-range of effect sizes reported in a meta-synthesis of meta-analyses of behaviour change interventions in the general population [57]. We will recruit two Year 8 classes (12–13 years) from 50 schools allowing for drop-out, though in previous LifeLab studies only one school has ever dropped out. To minimise bias from loss of students to follow-up, we will request class lists for each participating class, so that missing participants at each stage of the follow-up can be identified and included in secondary analyses and process evaluation assessing uptake of the intervention.

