### Randomisation/blinding

After signed agreement from the schools has been obtained and the classes taking part have been identified, schools will be randomised to receive usual schooling (control) or the EACH-B intervention (LifeLab programme, HCS training for teachers, and access to the digital intervention) (see Fig. 1). We will use a minimisation procedure developed by the Southampton Clinical Trials Unit (TENALEA), which aims to achieve a balance of schools in the two arms based on the following three criteria:
The proportion of students in the school receiving free school meals (cut-off > 24%);The proportion of students in the school achieving L5 GCSE (equivalent to a high ‘C’ grade) in English and Maths (cut-off > 40%);Whether or not the school already participated in the full LifeLab programme in the previous 2 years.

The randomisation is administered through a web-based secure system to which the EACH-B team submit the details of schools who have consented to participate. These are sequentially numbered and the allocation to intervention or control is then reported to the investigators. Blinding from this point onwards is not possible except of the statisticians who will be analysing the data.

Many schools we recruit will have previously been involved in LifeLab. Contamination of the intervention effect is unlikely to occur as the Year 8 students taking part in EACH-B will not have visited LifeLab before, and except for siblings, they will generally have limited contact with older children in the school. It will not be possible to blind schools and their students to their allocation due to the nature of the intervention.

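### Apart from the baseline outcome, the primary-model covariates are chosen from observed baseline imbalance, and the minimisation factors are not named among them

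*Protocol article*

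**What the plan says.** All references are to the protocol article.

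- **Primary model (Statistical methods).** Intention-to-treat comparison of dietary quality and physical activity, "using mixed effects linear regression to account for clustering within schools".
- **Trigger for adding covariates (same section).** After noting that schools are allocated by minimisation, the text warns that "there may still be disparities between the intervention and control participants at baseline". It continues: "These will be assessed prior to analysis and relevant confounders will be incorporated in the models".
- **Candidates (same section).** "factors to be considered include gender, exact age at recruitment and household area of deprivation", the last measured by the IDACI score. The wording is open-ended and commits to none of them.
- **Fixed covariate (the next sentence).** "Adjustment for baseline dietary quality and PA levels will be included in the relevant models to allow an assessment of change from baseline". This holds whatever the imbalance.
- **Minimisation (Randomisation/blinding).** The procedure is one "which aims to achieve a balance of schools in the two arms based on the following three criteria": free school meals above 24%, L5 GCSE attainment above 40%, and full LifeLab participation in the previous two years. The statistical methods section does not name these three as model covariates.

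**The concern.** When schools are randomised, the standard error already allows for chance differences between arms. A covariate earns its place in the primary model by predicting the outcome, which can be judged before any data are seen. A rule triggered by observed disparity has three weaknesses here.

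1. The model for both co-primary outcomes is not settled until baseline data have been compared by arm. Two analysts following the text could reach different models, because neither a threshold nor a closed list is given.
2. A prognostic factor that happens to be balanced can be left out, although adjusting for it would still improve precision.
3. Minimisation forces balance on three school-level factors. If these predict the outcome, a model without them does not credit that balance, and its standard error tends to be too wide. An imbalance screen would rarely bring them in, because minimisation is designed to remove their imbalance.

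At stake are the reproducibility of the primary estimate and some precision.

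**Working it through.** **Step 1: the protocol's own power figure.** Inputs from Sample size: 46 schools, about 50 students each (1150 per arm), a stated value that "indicates an intra-school (class) correlation coefficient of 0.035", a difference of 0.25 SD and 90% power. The significance level is printed as 0.025%. It is read here as 0.025 (0.05 split over two outcomes), two-sided, because the literal figure gives a power of only 0.490.

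- Design effect = 1 + (50 − 1) × 0.035 = 2.715.
- Standard error in SD units = √(2 × 2.715 / 1150) = 0.0687.
- Power = Φ(0.25 / 0.0687 − 2.241) = Φ(1.397) = 0.919. With a t reference on 46 − 2 = 44 degrees of freedom it is 0.902.

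The stated 90% is reproduced with no covariate in the model, so it does not depend on how covariates are chosen.

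**Step 2: what the covariates left to choice could add.** The protocol gives no correlations, so these are assumptions: baseline-outcome correlation r of 0.3 to 0.7; gender, age and IDACI together explaining a share q of 1% to 10% of the remaining variance; the same proportional reduction within and between schools. The variance is multiplied by (1 − r²) for the baseline outcome, and by a further (1 − q) if the three covariates are also fixed.

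Power at 0.25 SD (normal approximation, two-sided 0.025; 0.919 unadjusted):

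| r | Baseline outcome only | Plus the three, q = 1% | Plus the three, q = 10% | Added by the three |
|---|---|---|---|---|
| 0.3 | 0.942 | 0.944 | 0.962 | 0.2 to 2.0 points |
| 0.5 | 0.975 | 0.976 | 0.986 | 0.1 to 1.1 points |
| 0.7 | 0.998 | 0.998 | 0.999 | 0.0 to 0.1 points |

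Example for r = 0.5, q = 10%: variance factor 0.75 × 0.90 = 0.675; standard error 0.0687 × √0.675 = 0.0565; power Φ(0.25 / 0.0565 − 2.241) = 0.986.

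At a smaller true effect of 0.20 SD (0.748 unadjusted), the three covariates add about 0.2 to 4.4 points, against 4.3 to 21.8 points from the baseline outcome that the plan already fixes.

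**Step 3: type I error.** The protocol states no selection threshold. A 5% screen on three independent covariates was assumed for illustration, with 46 schools, r = 0.5 and the baseline outcome always in the model. By chance alone, such a screen picks at least one covariate in 1 − 0.95³ = 14% of trials. Simulated type I error was 0.024 to 0.026 with selection and 0.024 to 0.027 with fixed adjustment, against 0.025 nominal.

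**Step 4: cost of the fixed set.** Three binary school-level factors reduce the school-level degrees of freedom from 44 to 41. If they explained nothing at all, the t-based power in Step 1 would move from 0.902 to 0.900.

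**The case against.** The strongest reply is that little is at risk.

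- **The most important covariate is already fixed.** This stands, and it is why the loss is small. A reader might infer that the rule gives up most of the power obtainable from adjustment. The documents do not support that: the baseline outcome enters unconditionally, and the stated 90% needs no adjustment.
- **No false-positive cost.** This also stands. A reader might expect data-dependent selection to inflate type I error, but the check shows no inflation, and the protocol gives no threshold from which to argue otherwise.
- **Blinded statisticians, and assessment before analysis.** Both limit choices driven by outcome results. Neither removes dependence on imbalance: comparing arms requires the grouping, even if it is coded.
- **The analysis plan may close the list.** It may, and an article need not print every covariate. But the article states a rule. A plan that follows the rule inherits its weakness, and one that fixes the set departs from the printed text.
- **Disparities may not be pure chance.** Schools know their allocation, and the schedule figure is not shown, so participation differing by arm cannot be excluded. An imbalance screen would still be a weak safeguard, and a fixed prognostic set still preferable.
- **Season.** A reader might object that seasonality appears only among the subgroup analyses ("seasonal variation, IDACI score and estimated biological maturity in outcomes"). That adds little: follow-up is planned 12 months after baseline, so baseline adjustment should absorb part of a shared seasonal effect, and the open list does not exclude season.

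**Conclusion.** The point holds as a matter of pre-specification. Beyond the baseline outcome, the covariates of both primary models depend on observed imbalance, come from an open list without a criterion, and do not expressly include the minimisation factors. The precision forgone is about 0 to 2 percentage points of power at 0.25 SD. That range rests on the assumed correlations, on the 1% to 10% explained by gender, age and IDACI, and on equal proportional reduction within and between schools. The effect of omitting the minimisation factors has not been quantified, because the documents do not say how prognostic they are; the expected direction is conservative. The change is worth making because it settles the primary model in advance at almost no cost. The trial is not shown to be underpowered or its error rate compromised.

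**What to change.** Replace the sentence on assessing disparities with: *The primary models will adjust for the baseline value of the outcome, the three minimisation factors, gender, age at recruitment and IDACI, regardless of observed baseline imbalance.* Present baseline comparisons between arms descriptively only, with no role in choosing covariates, and carry the same list into the statistical analysis plan.

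Cost: one sentence and a few degrees of freedom. The minimisation factors are already known for every randomised school, and the other variables are ones the protocol already plans to consider or adjust for.

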**Methods:**

A cluster randomised controlled trial is being conducted to evaluate the effectiveness of the EACH-B intervention. The primary outcomes of the intervention are self-reported dietary quality and objectively measured physical activity (PA) levels, both assessed at baseline and at 12-month follow-up. The EACH-B intervention consists of three linked elements: professional development for teachers including training in communication skills to support health behaviour change; the LifeLab educational module comprising in-school teaching of nine science lessons linked to the English National Curriculum and a practical day visit to the LifeLab facility; and a personalised digital intervention that involves social support and game features that promote eating better and being more active.

Both the taught module and the LifeLab day are designed with a focus on the science behind the messages about positive health behaviours, such as diet and PA, for the adolescents now, in adulthood and their future offspring, with the aim of promoting personal plans for change. The EACH-B research trial aims to recruit approximately 2300 secondary school students aged 12–13 years from 50 schools (the clusters) from Hampshire and neighbouring counties. Participating schools will be randomised to either the control or intervention arm. The intervention will be run during two academic years, with continual recruitment of schools throughout the school year until the sample size is reached. The schools allocated to the control arm will receive normal schooling but will be offered the intervention after data collection for the trial is complete. An economic model will be developed to assess the cost-effectiveness of the EACH-B intervention compared with usual schooling.

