#### Personalised digital intervention

The digital intervention will be in the form of a mobile phone application (app) with game features. It has been developed using a person-based approach to intervention development, combined with user-centred design principles for digital game design and a participatory design process. The design of the game is underpinned by self-determination theory and employs a range of behaviour change techniques [33, 44, 45].

During the LifeLab visit, students will be asked to download the app onto their personal mobile devices (Android or IOS) and log in. Any student without a personal device will be given instructions for downloading the app at home via a shared family device. The app will involve creating a character and choosing games, quizzes and challenges to complete. Players can choose challenges and none are compulsory. The app will allow players to connect with each other if they wish. Parents/carers of students in the intervention will also be offered a companion app to help them support their adolescent in making healthy lifestyle choices. The parent app includes information about the different elements of the app developed for the young people taking part in the intervention. It also contains ideas, suggestions and prompts as to how parent and adolescent can join forces to improve food choices and activity levels for the whole family.

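### The per-protocol estimate in students who fully engage with the app is not protected by randomisation and should not be presented as an effect of EACH-B

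*Protocol article*

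**What the plan says.** In the Protocol article, Statistical methods, the primary comparison is fixed first: "The primary analyses will be according to the intention-to-treat principle", using mixed effects linear regression. On covariates the section adds: "Adjustment for baseline dietary quality and PA levels will be included in the relevant models". After the subgroup analyses comes the sentence at issue: "We will also determine the effect of EACH-B on outcomes for those who fully engage with the digital intervention (per protocol analysis". The next sentence plans CACE modelling, among other things "to examine intervention effects specifically for students who engaged with those components", and the article then warns that "many of the assumptions underlying this method are unlikely to be valid, most obviously the independence of the participants".

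Three other places bear on this. Personalised digital intervention says of the app: "Players can choose challenges and none are compulsory". The Methods part of the abstract says that control schools "will receive normal schooling but will be offered the intervention after data collection for the trial is complete". Trial design and The intervention describe three components: trained teachers, the LifeLab module with its day visit, and the app.

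**The concern.** Whether a student fully engages with the app is that student's own choice, made after allocation. Control students do not have the app during the trial, so those among them who would have engaged cannot be identified. Any direct contrast with controls sets a self-selected part of one arm against students who were not selected in that way. Students already inclined to eat better or move more are plausibly the ones who keep using a health app, so the likely bias favours the intervention.

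The label adds to the difficulty. App challenges are optional and the app is one component of three. A student who attends every lesson and the LifeLab day but uses the app little has not departed from the protocol. The analysis conditions on one voluntary component yet attributes the result to EACH-B as a whole. At stake is a supplementary estimate that readers could take as the effect of EACH-B when used as intended.

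**Working it through.** **Step 1: the plan's own design figure.** Inputs from Sample size: a 0.25 SD difference, 90% power, intra-school correlation 0.035, 46 schools of about 50 students. The significance level is printed as 0.025% and read here as 0.025 (0.05/2 for two primary outcomes), two-sided.

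- Individually randomised size: 2 × (2.241 + 1.282)² / 0.25², which gives 398 per arm.
- Variance inflation: 1 + 49 × 0.035 = 2.715.
- Total: 2 × 398 × 2.715 = 2161 students, or 22 schools per arm. One further school per arm as a small-sample correction gives 46 schools and 2300 students.
- Power at 2300: 91.9% (normal) or 90.2% (t, 44 df).

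The design reproduces. The yardstick is the difference it was built "to detect a 0.25 SD difference in diet quality score or minutes of total PA in intervention and control schools".

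**Step 2: bias with no true effect.** The article gives none of the following, so they are assumptions:

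- p, the share of intervention students who fully engage;
- rho, the correlation of engagement tendency with the outcome;
- r, the baseline to follow-up correlation of the outcome.

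The comparator is assumed to be all control students. With normal variables and z the cut-off leaving a share p above it:

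- unadjusted bias = rho × phi(z)/p;
- baseline-adjusted bias = rho × (1 − r) × phi(z)/p, if engagement correlates equally with the baseline and follow-up outcome.

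At p = 30%, phi(z)/p = 1.159. For rho = 0.2 the unadjusted bias is 0.2 × 1.159 = 0.23 SD. For rho = 0.3 it is 0.3 × 1.159 = 0.35 SD. With r = 0.5 these become 0.116 and 0.174 SD.

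**Step 3: simulation check.** 23 schools per arm of 50 students, intra-school correlation 0.035, true effect zero, 300 runs per setting, two-sided level 0.025, p = 30%, r = 0.5:

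| rho | Unadjusted: mean bias; rejections | Adjusted: mean bias; rejections | Intention-to-treat: rejections |
|---|---|---|---|
| 0.2 | 0.227 SD; 69% | 0.112 SD; 21% | 2% |
| 0.3 | 0.339 SD; 95% | 0.169 SD; 57% | 3% |

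With p = 30%, rho = 0.3 and r = 0.7, the adjusted bias was 0.106 SD with 31% rejections.

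**Step 4: correlation needed for a false benefit of 0.25 SD.**

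| p | Unadjusted | Adjusted, r = 0.5 | Adjusted, r = 0.7 |
|---|---|---|---|
| 20% | 0.18 | 0.36 | 0.60 |
| 30% | 0.22 | 0.43 | 0.72 |
| 50% | 0.31 | 0.63 | not attainable |

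**Step 5: does CACE answer the question?** In the same simulations the intention-to-treat difference divided by p (a simple CACE) averaged close to zero, at most 0.03 SD in size. In those runs no component had any effect, so the exclusion restriction held. It is doubtful if compliance means app engagement alone, because students who do not use the app still receive the lessons, the LifeLab day and trained teachers. As an illustration, suppose those components produced the full 0.25 SD in every intervention student and the app added nothing. An app-defined CACE at p = 30% would then report 0.25 / 0.30 = 0.83 SD, although the effect in engagers is 0.25 SD. The article names independence as the doubtful assumption and does not mention this one.

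**The case against.** The strongest reply has four parts.

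**The comparator is inferred.** The article names no comparator, model or covariates for this analysis, and such detail may properly sit in the full protocol or the analysis plan. This stands, and the absence of those details is no finding. The point does not depend on them: however full engagement is defined, it is a post-randomisation choice seen in one arm only.

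**CACE is planned in the next sentence.** It uses randomisation to reach the effect in students who engaged, and the article says its assumptions will be assessed. One could read the first sentence as the question and the CACE sentence as the method. That is possible, but the text names a per-protocol analysis separately and says that the effect will also be determined. A reader might infer that the authors overlooked selection altogether; the planned CACE and its caveat do not support that.

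**The size is assumed, and baseline adjustment reduces it.** This stands. If the planned adjustment applies here, it halves the bias at r = 0.5. It cannot remove motivation to change that baseline behaviour does not yet show. If 0.2 is instead the correlation left after adjustment, 0.232 is in residual SD units. It converts to 0.232 × √(1 − 0.5²) = 0.20 outcome SD at r = 0.5, or 0.232 × √(1 − 0.7²) = 0.17 at r = 0.7.

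**The analysis is supplementary.** This stands too. The primary analysis is by intention to treat, and neither the sample size nor the primary error rate depends on the per-protocol result.

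**Conclusion.** The concern holds in a limited form. The article commits to an effect estimate in a self-selected group observable in one arm only, and a direct contrast of that group with controls can show a benefit when none exists. With no true effect, 30% engaged and a correlation of 0.2 to 0.3, the false benefit is about 0.23 to 0.35 SD unadjusted, or about 0.11 to 0.17 SD with baseline adjustment at r = 0.5. Even the adjusted contrast rejected in 21% to 57% of simulated null trials, against 2% to 3% for intention to treat. All of this assumes that the comparator is all controls.

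A reader might infer that the analysis will manufacture a benefit as large as the 0.25 SD target. The documents do not support that as a general statement. They give no engagement rate or correlation, and after adjustment that size needs low engagement together with a strong correlation, such as 20% and 0.36 at r = 0.5. Nor does the point cast doubt on the primary intention-to-treat result.

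**What to change.** 1. Do not present the per-protocol contrast as an effect of EACH-B. Either drop it, or keep it labelled as descriptive and non-randomised, with its comparator and covariates stated.
2. Report app engagement within the intervention arm, alongside the uptake summaries by gender, ethnicity and deprivation score that are already planned.
3. Answer the question of the effect when the intervention is received with the planned CACE analysis, accounting for clustering. Define compliance as receipt of the intervention package rather than app engagement alone, and list the exclusion restriction among the assumptions to be assessed.

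The cost is a change of wording in the protocol or analysis plan. No new data are needed, and the sample size and primary analysis stay as they are. The downside is that one supplementary estimate is lost or relabelled.
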